## Abstract

**Background::**

Lower urinary tract symptoms associated with benign prostatic hyperplasia (LUTS/BPH) are one of the most common conditions seen in middle-aged and elderly men and threaten their quality of life. Since conventional pharmacotherapy for LUTS/BPH can lead to sexual side effects, herbal therapies are widely used as complementary and alternative treatments worldwide. HT080 is an herbal extract of *Cinnamomum cassia* and *Rosa Laevigata*, both of which have been used to treat symptoms typically associated with BPH in traditional Asian medicine. The aims of this trial are to assess whether HT080 can alleviate LUTS/BPH in middle-aged and elderly men, and to investigate the safety of HT080.

**Methods/design::**

A double-blind, randomized, placebo-controlled, two-arm parallel group trial will be conducted in men with moderate LUTS/BPH. A total of 100 eligible men aged 40 to 75 years with an International Prostate Symptom Score of 8 to 19 will be randomized in a 1:1 ratio and receive either HT080 (500 mg) or placebo twice a day for 12 weeks. All participants will be evaluated for efficacy and safety at baseline and weeks 6 and 12. The primary endpoint is the change in International Prostate Symptom Score between baseline and week 12. The secondary efficacy variables are uroflowmetry parameters (maximal urinary flow rate and post-void residual volume), serum prostate-specific antigen, testosterone, and dihydrotestosterone levels, the International Index of Erectile Function score, and participant-reported global response assessment scores. The safety assessments include adverse events, laboratory tests results, vital signs, and physical examination.

**Discussion::**

This is a first-in human trial designed to investigate the efficacy and safety of HT080 among middle-aged and elderly men with LUTS/BPH. This prospective study with a double-blind randomized design will provide high-quality evidence supporting the use of HT080 for LUTS/BPH.

**Trial registration::**

Korean Clinical Research Information Service (KCT0004286) Registered September 6, 2019.

## Introduction

1

Lower urinary tract symptoms (LUTS) are common in middle-aged and elderly men and significantly impair the quality of life.^[1]^ LUTS include storage, voiding, and post-micturition symptoms inducing increased frequency, nocturia, incontinence, weak stream, hesitancy, intermittency, straining to void, terminal dribble, and a sensation of incomplete bladder voiding. LUTS in men generally results from benign prostatic hyperplasia (BPH) which is characterized by hyperproliferation of epithelial and stromal cells of the prostate. The global prevalence of BPH has rapidly increased with aging in the population, thus becoming an economic burden.^[2]^ In Korea, the prevalence of BPH in 2016 increased 2.2-fold that in 2012 and approached 37.5% and 53.8% among men in their 60s and in those above 80 years of age, respectively.^[3]^

Treatment options for LUTS associated with BPH (LUTS/BPH) include watchful waiting, lifestyle modification, medications, and surgery.^[4]^ Two classes of drugs, α-adrenergic receptor blockers and 5α-reductase inhibitors, are used for pharmacotherapy. Unfortunately, these drugs are associated with sexual side effects, including ejaculatory disorders for α-adrenergic receptor blockers and erectile dysfunction, ejaculatory dysfunction, and decreased libido for 5α-reductase inhibitors.^[5]^ This has led a to an increased demand of herbal therapies (*Serenoa repens*, *Pygeum africanum*, *Hypoxis rooperi*, etc.) as complementary and alternative treatments among numerous patients worldwide.^[6,7]^ In Europe and the USA, about half or more of BPH patients use herbal therapies alone or with other drugs.^[6,8]^ In Asian countries including China and Korea, traditional herbal medicine has been used to treat BPH for hundreds of years, and is still commonly used to this day.^[9–11]^

HT080 is an herbal extract of *Cinnamomum cassia* bark and *Rosa laevigata* fruit. It was developed by screening various herbs used in traditional Asian medicine for the treatment of LUTS, with the aim of reducing prostate smooth muscle tone and prostate growth. These two herbs have been traditionally prescribed in combination to treat symptoms typically associated with BPH including frequent urination and nocturia in China.^[12,13]^*C cassia*, commonly called Chinese cassia or cassia cinnamon, is an evergreen tree that originated in southern China and is now cultivated in eastern and southern Asia for its bark, cinnamon. In traditional Korean, Chinese, and Ayurvedic medicine, the bark of *C cassia* has been widely used to treat frequent urination, nocturia, difficulty in urinating, and a weak urine stream in middle-aged and elderly men.^[7,10,14,15]^ A systematic review reported that *C. cassia* is the most frequently used single herb in Chinese herbal medicine for BPH and was used in 17 (54.8%) of 31 studies.^[10]^ Concurrent with these clinical applications, cinnamic acid, the major component of *C cassia*, serves as a potent antagonist of the α_1A_-adrenoceptor in the rat prostate.^[16]^ Furthermore, *C verum*, which is used as a substitute for *C cassia* and vice versa, has reportedly reduced testosterone-induced BPH by downregulating 5α- reductase and androgen receptor expression.^[17]^*R laevigata* is a climbing shrub originating from South China and Southeast Asia, and its fruit has been used to treat frequent urination, urinary incontinence, and sexual dysfunction in traditional Chinese and Korean medicine.^[18,19]^*R Laevigata* reportedly decreases the voiding frequency and increases the inter-micturition interval and urine volume by inhibiting smooth muscle contraction in a mouse pollakiuria model.^[20]^ Furthermore, *R laevigata* has been shown as one of the most potent 5α-reductase inhibitors in a screening assay for anti-5α-reductase, including 162 plants.^[21]^ Although traditional use and preclinical findings support the applications of HT080, a well-designed prospective clinical trial has yet to be conducted to evaluate the efficacy and safety of HT080.

### Objectives

1.1

This trial primarily aims to determine whether HT080 is superior to the placebo for reducing LUTS, as measured on the basis of the International Prostate Symptom Score (IPSS), in middle-aged and elderly men with moderate LUTS/BPH. The secondary objectives are to investigate the effects of HT080 on uroflowmetry parameters and androgen levels, and to assess the safety of HT080. The exploratory objective is to evaluate whether HT080 affects sexual function.

### Design

1.2

This study is a double-blind, randomized, placebo-controlled, superiority trial with two parallel groups. Eligible participants will be randomly assigned to either the HT080 or placebo group with a 1:1 allocation ratio and will receive the investigational product for 12 weeks.

## Methods and design

2

### Study setting

2.1

Participants will be recruited from Department of Urology, Yonsei University Severance Hospital (Seoul, Republic of Korea). The estimated recruitment period will be 1 year beginning from October 2019. The recruitment will be advertised on hospital bulletin boards and websites. Monthly newsletters will be sent to encourage enrollment until the required sample size is achieved. The first participant has not been enrolled yet.

### Eligibility criteria

2.2

Following will be the inclusion criteria for the study:Men aged 40–75 yearsAn IPSS of 8–19Prostate size ≥ 20 gAvailability of written informed consent to participate in the study.

Following will be the exclusion criteria for the study:Current treatment for clinically significant acute or chronic cerebrovascular, immune, respiratory, hepatobiliary, kidney and urinary, neurological, musculoskeletal, psychiatric, infectious, or hemato-oncological diseases. (However, inclusion/exclusion from the trial will be at the investigators’ discretion based on participants’ condition).Serum prostate-specific antigen level ≥ 10 ng/mL. (However, participants in whom test results are not definitively confirmed as cancer within 6 months prior to study enrollment will be eligible for inclusion in the study).Maximal urinary flow rate < 5 mL/sPost-void residual urine volume > 200 mLBladder tumors, urinary stones, urethral strictures, bladder neck contracture, inflammation of the lower urinary tract (bladder and urethra), or urinary tuberculosisDiagnosis of prostate cancerHistory of genitourinary surgery, including prostate surgery or other invasive procedures for treatment of prostatic conditions (transurethral needle ablation, and laser treatment, among other such therapies)Uncontrolled hypertension (systolic blood pressure ≥ 160 mmHg or diastolic blood pressure ≥ 100 mmHg measured after a 10-min rest)Uncontrolled diabetes (fasting blood glucose level ≥ 180 mg/dL or administration of drugs for diabetes within the preceding 3 months)Thyroid diseasesSerum creatinine level > 2-fold the upper limit of normalAspartate and alanine aminotransferase levels ≥ 3-fold the upper limit of normalAdministration of drugs (antimuscarinics and/or others) for benign prostatic hyperplasia (BPH) or intake of functional foods within the preceding 4 weeksParticipation in other clinical trials within the preceding 3 months or plans to participate in other trials during the present study.Unsuitability for study participation based on the investigator's discretion.

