### Procedures

2.3

This trial is designed to provide treatment with either HT080 or placebo in subjects with LUTS/BPH and assess symptom improvement during 12 weeks of treatment. The flow diagram is shown in Figure 1 and the schedule for enrollment, interventions, and assessment of this study is summarized in Table 1. The principle investigator will obtain written informed consent from subjects who voluntarily agreed to participate in this trial before eligibility assessment. After applying inclusion and exclusion criteria, eligible participants will undergo baseline assessments within 14 days of screening visit. Following the administration of HT080 or placebo, participants will visit the hospital at weeks 6 and 12 (visit window ± 7 days) and evaluated for efficacy and safety of the investigational product as shown in Table 1. A 24-hour dietary recall questionnaire will be used on 3 random days during the last week of each time point at baseline and at weeks 6 and 12 to investigate participants’ usual dietary pattern during the trial.

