### Interventions

2.4

The investigational product will be provided by COSMAX BIO Inc. (Jecheon, Chungcheongbuk-do, Republic of Korea). The active product is a 500 mg tablet containing 250 mg of HT080 (60 mg of *C cassia* extract and 190 mg of *R laevigata* extract). To ensure blinding, the placebo tablet will be of the same size, shape, and color as the active tablet. Participants will be orally administered 2 active or placebo tablets twice daily (morning and evening before meals) for 12 weeks. HT080 will be administered at a dose of 1000 mg daily. The investigational product will be packaged as a 6-week supply and will be prescribed to participants at baseline and week 6. To improve the adherence to the treatment, participants will be encouraged to adhere to the prescribed dosage regimen, and compliance will be evaluated by counting the number of unused tablets returned at 6 and 12 weeks.

The following treatments will be prohibited during the trial period: drugs such as 5α-reductase inhibitors and α-blockers administered for BPH, drugs administered for nocturnal enuresis or erectile dysfunction, antimuscarinic agents and supplements for prostate health, and procedures such as transurethral needle ablation, prostatectomy, and laser treatment. Intake of functional foods and medications administered before study participation and agents that are not expected to affect the trial results may be permitted at the investigator's discretion. Drugs used for short-term treatment of other diseases will be co-administered after consultation with the investigator. Participants will be instructed to continue their usual dietary pattern and physical activity habits during the trial period and avoid the consumption of products containing *C cassia* and/or *R laevigata*. Concomitant medications and therapies will be monitored at 6 and 12 weeks.

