Criteria for discontinuing intervention will include the following:1.violation of inclusion or exclusion criteria,2.detection of a systemic disease that had not been identified during participant screening,3.discontinuation of participation following notice of withdrawal by the participant or his/her legal representative because of unsatisfactory trial results or adverse events during the study period,4.withdrawal of consent to participate,5.loss to follow-up,6.difficulty with administration of the investigational product,7.intake of other medications, such as 5α-reductase inhibitors, α-blockers, and antimuscarinics that could affect the results of this trial, and (8) trial discontinuation is deemed necessary by the investigator.

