### Outcome measures

2.6

The Korean IPSS questionnaire will be used to assess the primary endpoint. The IPSS, which has been used for decades to assess the severity of LUTS/BPH, contains seven questions on voiding symptoms (incomplete emptying, intermittency, weak stream, and straining) and storage symptoms (frequency, urgency, and nocturia).^[22]^ Each item is scored 0 to 5, giving a maximum total score of 35. A total score of 0 to 7 indicates mild symptoms, 8 to 19 indicates moderate symptoms and 20–35 indicates severe symptoms. Participants will complete the IPSS questionnaire at screening, baseline, and weeks 6 and 12. The primary efficacy endpoint is the change in IPSS at week 12 from the baseline.

As the secondary outcomes, uroflowmetry parameters (maximal urinary flow rate and post-void residual volume) and serum prostate-specific antigen, testosterone, and dihydrotestosterone levels will be measured at screening and weeks 6 and 12. Global response assessment will be completed by participants at weeks 6 and 12 using a five-point scale (markedly worsened, worsened, unchanged, improved, and markedly improved). It has been reported that 70% of BPH patients has an associated erectile dysfunction.^[23]^ Participants will complete the International Index of Erectile Function questionnaire, a multi-dimensional self-report instrument widely used to evaluate male sexual function,^[24,25]^ at baseline and weeks 6 and 12. The safety outcome measures include adverse events, laboratory tests (hematology, biochemistry, and urinalysis) results, vital signs, and physical examination.

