### Withdrawal and dropout

2.11

Participants may withdraw from the trial at any time for any reason. The investigator may also withdraw participants from the trial due to medical or administrative reasons (adverse events, continuous protocol violations, etc.). Reasons for withdrawal and dropout will be recorded in the case report form.

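### The exception to the PSA ≥ 10 ng/mL exclusion is worded so that a recent inconclusive or suspicious result is not excluded by that criterion; probably a misplaced negation, minor

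*Protocol article*

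**What the plan says.** Section 2.2 (Eligibility criteria) lists a serum PSA of at least 10 ng/mL as an exclusion and qualifies it at once in brackets: "participants in whom test results are not definitively confirmed as cancer within 6 months prior to study enrollment will be eligible". Nothing else in the article restates or corrects this exception.

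The same section has two other exclusions that bear on these men. Diagnosed prostate cancer is excluded in its own right, and a general clause covers "Unsuitability for study participation" at the investigator's discretion.

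After enrolment, section 2.4 (Interventions) lists grounds for stopping treatment, among them "violation of inclusion or exclusion criteria" and the case where "trial discontinuation is deemed necessary by the investigator". Section 2.11 (Withdrawal and dropout) adds: "The investigator may also withdraw participants from the trial due to medical or administrative reasons". Section 2.6 (Outcome measures) provides for repeat PSA: "serum prostate-specific antigen, testosterone, and dihydrotestosterone levels will be measured at screening and weeks 6 and 12".

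**The concern.** A PSA threshold in a BPH trial serves to keep out men whose raised value may reflect cancer. An exception makes sense for men who have been worked up and in whom cancer was ruled out. The printed exception sets a different test: it is met when cancer has not been definitively confirmed. An inconclusive result meets that test, and so does a suspicious one.

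Two things are at stake. One is the safety of a man who would start 12 weeks of trial treatment with an unresolved suspicion of cancer. The other is whether the enrolled men are the BPH population that the trial means to study.

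**Working it through.** No arithmetic applies; the check is one of wording. It compares three meanings of the exception for men with PSA ≥ 10 ng/mL:

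- **Probable intended meaning:** a result within 6 months has confirmed that there is no cancer.
- **Printed words, test presupposed:** a test was done within 6 months, and its result did not definitively confirm cancer.
- **Printed words, fully literal:** no definitive confirmation of cancer exists from the last 6 months, whether or not a test was done.

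| Man with PSA ≥ 10 ng/mL | Probable intended meaning | Printed, test presupposed | Printed, literal |
|---|---|---|---|
| Cancer confirmed within 6 months | excluded | excluded | excluded |
| Cancer ruled out within 6 months | not excluded | not excluded | not excluded |
| Inconclusive or suspicious result within 6 months | excluded | **not excluded** | **not excluded** |
| No test within 6 months | excluded | excluded | not excluded |

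The third row carries the point, because its answer is the same on both printed readings and changes only when the negation is moved.

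The first row explains why the negation looks misplaced. A man with confirmed cancer is already kept out by the separate exclusion for diagnosed prostate cancer. As printed, the PSA criterion therefore largely overlaps with that exclusion, and a numeric threshold would hardly have been written for that purpose.

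Next, which other provisions could keep the third-row man out?

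1. The separate cancer exclusion does not, because he has no diagnosis.
2. The stopping ground "violation of inclusion or exclusion criteria" does not, because a man admitted under the printed exception has violated no criterion.
3. The unsuitability clause can, before enrolment, if the investigator so judges.
4. The ground that "trial discontinuation is deemed necessary by the investigator" and the medical withdrawal in section 2.11 can, after enrolment, again by judgement.

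What is left is discretion. No stated rule requires cancer to be ruled out.

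**The case against.** The strongest reply is that this is a translation or drafting slip in a condensed article. The sites follow the approved protocol (ver. 1.0, cited in section 2.12), which is not shown and may be worded correctly. The redundancy noted above is itself a reason to doubt that the investigators mean, or would apply, the printed words. Men are recruited in a urology department, PSA is repeated at weeks 6 and 12, and the investigator can exclude or withdraw a man on medical grounds. Work-up is not blocked either, since the prohibited "procedures such as transurethral needle ablation, prostatectomy, and laser treatment" are treatments and not diagnostic steps.

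Most of this stands, and it limits the weight of the point. It does not make the sentence right: eligibility rules are applied and monitored as written, and discretion does not replace a stated rule.

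A reader might infer several stronger claims, which the article does not support:

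- **Untested men are let in.** One could argue that a man whose raised PSA first appears at screening may go straight on, given that "eligible participants will undergo baseline assessments within 14 days of screening visit". This needs the fully literal reading. A clause that speaks of test results in a 6-month window more naturally presupposes a work-up in that window.
- **The threshold excludes no one beyond diagnosed cancer.** This rests on the same literal reading. With a test presupposed, untested men stay excluded.
- **Men with a suspicious result qualify for the trial.** They pass one criterion; every other exclusion, including unsuitability, still applies.
- **The efficacy results are affected.** No mechanism for a between-arm bias in IPSS follows from the wording, and none has been shown for PSA as a secondary outcome.

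**Conclusion.** The exception is wrong as written, and the point is minor. On either reading of the printed words, a man with PSA ≥ 10 ng/mL and an inconclusive or suspicious result from the last 6 months is not excluded by this criterion. Only the separate cancer-diagnosis exclusion and the investigator's judgement remain, and the first does not reach him while he is undiagnosed.

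The size cannot be given. The article does not say how many of the 100 planned men would have a PSA this high, and there may be none. No effect on the IPSS comparison, on balance between the arms or on the sample size is claimed.

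Two assumptions matter. That the negation is misplaced is an inference; it is well supported by the overlap with the cancer exclusion, but the article does not state it. That the approved protocol carries the same words is unknown; if it already requires cancer to be ruled out, the error lies in the article alone.

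**What to change.** Check the sentence in the approved protocol. If it reads as in the article, reword it before first enrolment, for example: *Serum PSA ≥ 10 ng/mL, unless an existing documented result from the 6 months before enrolment rules out prostate cancer.* Inconclusive, suspicious or pending results would then not satisfy the exception.

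Keep the exception and do not delete it. An allowance for men with a raised PSA in whom cancer has been ruled out was probably intended, and deletion would remove it. Which test counts can be left to the investigators.

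The cost is one sentence, plus an amendment if the approved text has the same wording. No new procedure is needed. Section 2.1 states that nobody had been enrolled at the time of writing, so no randomised man is affected. The downside is that a few men with PSA ≥ 10 ng/mL and an unresolved result become ineligible; under the probable intended rule they were never meant to enter. If the approved protocol is already correct, a correction to the article is enough.

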### Procedures

2.3

This trial is designed to provide treatment with either HT080 or placebo in subjects with LUTS/BPH and assess symptom improvement during 12 weeks of treatment. The flow diagram is shown in Figure 1 and the schedule for enrollment, interventions, and assessment of this study is summarized in Table 1. The principle investigator will obtain written informed consent from subjects who voluntarily agreed to participate in this trial before eligibility assessment. After applying inclusion and exclusion criteria, eligible participants will undergo baseline assessments within 14 days of screening visit. Following the administration of HT080 or placebo, participants will visit the hospital at weeks 6 and 12 (visit window ± 7 days) and evaluated for efficacy and safety of the investigational product as shown in Table 1. A 24-hour dietary recall questionnaire will be used on 3 random days during the last week of each time point at baseline and at weeks 6 and 12 to investigate participants’ usual dietary pattern during the trial.

